## Abstract

**Background:**

African American men are at a higher risk for serious health conditions such as cardiovascular disease, diabetes, and stroke compared to non-Hispanic White men. Physical activity (PA) is a modifiable health behavior that has been shown to decrease chronic disease risk; yet, PA engagement is alarmingly low in African American men. Interventions to improve PA engagement are effective in a number of populations; however, very few have been tailored to the unique needs of African American men. Even fewer have leveraged mobile health apps, despite African American men’s interest in and willingness to use such technologies for health improvement.

**Objective:**

This comparative effectiveness trial aims to evaluate MobileMen, a PA promotion app tailored to the needs and preferences of African American men. This trial will compare the MobileMen app to a commercially available PA promotion app with similar features but lacks culturally tailored components.

**Methods:**

We will recruit a sample of “low active” (accumulating <7500 steps per day) African American men (n=100) aged >30 years from Baton Rouge, Louisiana, and the surrounding communities. All participants are given a Fitbit Charge 6 wearable activity tracker to assess daily PA and steps and are randomized to either the MobileMen intervention app or the comparator app, which is a commercially available PA tracking app called Stridekick. The Stridekick app has features similar to those in the MobileMen app but was not intentionally designed for African American men. The intervention period is 6 months during which participants will interact with their assigned mobile app. MobileMen includes features such as digital badges earned for PA; tangible prizes like exercise equipment; challenges among participants; goal setting; nutrition; PA; and behavior change educational information in text, audio, and video formats. Participants will complete assessments at baseline and at 6 months post randomization. Assessments include objective measurements of daily steps and minutes of moderate to vigorous PA, quality of life, dietary measures, self-efficacy for fruit and vegetable consumption and PA, and autonomous motivation for PA.

**Results:**

This trial is in the start-up phase. The MobileMen app development and usability testing was completed in August 2024. Participant recruitment efforts began in October 2024. The trial and associated data analyses and interpretation are planned to be completed by fall 2025.

**Conclusions:**

Mobile apps are a widely accessible means to disseminate culturally tailored PA promotion interventions to various populations, including African American men. MobileMen has the potential to impact PA engagement in African American men, which would dramatically improve the overall health and chronic disease risk in this underrepresented group.

**Trial Registration:**

ClinicalTrials.gov NCT05621044; https://clinicaltrials.gov/study/NCT05621044

**International Registered Report Identifier (IRRID):**

PRR1-10.2196/67809

## Introduction

African American men experience disproportionately high rates of obesity, cardiovascular disease, hypertension, stroke, diabetes, and prostate cancer compared to their non-Hispanic White counterparts [1-4]. Increased levels of physical activity (PA) and fitness have been associated with the reduced risk of these chronic conditions [5-11]. However, there is a lack of regular PA in the African American community, and African American men’s rates of PA are well below national guidelines [12-15].

Comparatively, research consistently shows that African American men engage in lower levels of PA than their non-Hispanic White counterparts. Although 48% of non-Hispanic White adults meet PA guidelines of 150 minutes of moderate to vigorous activity per week, only 39% of Black adults meet that guideline [16]. This disparity is due to a complex interplay of social, environmental, and cultural factors [13,14,17,18]. Black men are more likely to live in neighborhoods with limited access to safe recreational spaces and face greater exposure to crime, which discourages outdoor activity [19]. Socioeconomic constraints such as demanding work schedules and caregiving responsibilities further limit their leisure time for PA [20]. Cultural norms around family roles, along with a lack of culturally relevant health messaging, can reduce motivation or the perceived value of PA [21,22]. Additionally, experiences of racism and discrimination—both in everyday life and within health care—contribute to chronic stress, mistrust of health institutions, and lower engagement in preventive health behaviors, including PA [23]. These structural and psychosocial barriers collectively create significant obstacles to PA for Black men. Thus, novel interventions are needed to support PA initiation and persistence in this population.

Mobile health (mHealth), which is the use of mobile phones in providing medical care, has been increasingly used to change and maintain health behaviors such as PA across various populations [24-26]. Smartphones create enormous potential for intervention delivery because they are compact, portable, normally “on,” readily available to individuals, affordable, user-friendly, offer advanced functionality, and allow online access on demand any day or time [27-32]. mHealth interventions have been used to successfully increase PA across several settings and health conditions, including in health care settings and among cancer survivors [33-36].

African American men appear to have a positive attitude toward mHealth interventions, and approximately 44% of African American men who received 5 months of PA training were willing to receive an mHealth maintenance intervention [32]. This was especially encouraging because the sample had a mean age of 53 years, and mobile app usage and acceptability is typically lower in men 50 years of age and older [32]. African American men also demonstrated a willingness to engage in mHealth interventions specifically targeting chronic disease risk reduction [32]. Moreover, evidence suggests that mHealth interventions are effective with African American men. A recent study of a comprehensive health app for African Americans indicated that users improved their minutes of moderate PA after 10 weeks of use [37]. Other studies have utilized text messaging to influence health behaviors in African Americans, also resulting in increased PA [38,39]. However, the samples in these studies were mostly females, and none of the outcome data were analyzed by sex, further elucidating the need for the development and testing of mHealth interventions specific to African American men [37-39].

To address the gap in mHealth apps developed specifically for African American men, we developed, to the best of our knowledge, a first of its kind smartphone app, MobileMen, to support PA engagement in this population. The process for developing this app and the further rationale for the selected components are described elsewhere [40]. MobileMen is grounded in 2 behavior change theories: social cognitive theory (SCT) and self-determination theory (SDT). SCT states that the environment and a person’s behavior interact to shape behavior and that self-efficacy is the key component to behavior change [41]. SCT was the foundation of the PA adoption content focusing on self-monitoring, goal setting, and social support in the MobileMen app. We chose SCT because SCT-grounded interventions have been effective at increasing and maintaining PA in African Americans [42-47]. In addition, SDT posits that satisfying 3 fundamental needs contributes to behavior change: perceived competence, a feeling of relatedness (feeling connected to others), and autonomy (feeling that change is a choice and not coerced) [48-52]. When an activity fulfills these 3 needs, people can become more autonomously motivated, resulting in more PA initiation and persistence [53]. In African American men, specifically, intrinsic motivation associates PA engagement with personal values and overall health goals, increasing the likelihood that they will persist with the behavior [54]. In the MobileMen app, we included features such as reminders and goal setting to support the development of autonomy [55]. To support competence, we included activity history and feedback such as cumulative exercise statistics aggregated over weeks and months, logging of weight training workouts and health metrics, and tangible and digital rewards [55]. We also included the ability to participate in competitions with other users and a message function to support the basic need of relatedness [55].

Additionally, the MobileMen app was culturally tailored to African American men. The culturally tailored content was based on the model established by Kreuter et al [56] who describe 5 strategies to culturally tailor an intervention: (1) peripheral, (2) evidential, (3) linguistic, (4) constituent-involving, and (5) sociocultural. Peripheral strategies involve matching the materials and messaging to the observable characteristics of the target population (eg, utilization of images of African American men), analogous to face validity and like Resnicow et al’s [57] surface structure. Evidential strategies seek to put into context the health impact for a target population (eg, notifications such as “African American men have higher rates of diabetes compared to men from other ethnic groups. Engaging in regular PA can reduce your risk of developing diabetes”). Linguistic strategies involve using language to make materials more accessible to the target audience (eg, Beast Mode badge). Constituent-involving strategies are informed by experiences or input from the population of interest (eg, utilizing focus groups with African American men). Sociocultural strategies reflect the underlying beliefs, values, and norms of a group, like Resnicow et al’s [57] deep structure. Sociocultural strategies involve how cultural, social, psychological, environmental, and historical factors affect health behaviors specifically within the target population. It is concerned with the target population’s conceptualization of the need for intervention and accurate incorporation of this information into the treatment model. Commonly noted facilitators of PA include the need for peer support and camaraderie specifically from men and competition [58,59]. African American men’s gender role responsibility and commitment to family, friends, and community also play a role in the adoption and maintenance of PA. Although the men noted these factors during focus groups for the development of the app, they could not be incorporated into the prototype due to the limited scope. However, these factors largely contribute to the current app development. For example, educational content was included that explicitly acknowledges gender role expectations and provides practical strategies based on SCT (eg, cognitive restructuring, social support techniques) and SDT (eg, fostering relatedness through competition) to assist men with incorporating family and friends into PA as part of the adoption and maintenance strategies.

The purpose of this paper is to describe the study protocol for examining the effectiveness of MobileMen. This trial will test the hypothesis that the MobileMen app will increase PA in African American men in comparison with Stridekick, a popular fitness app.

## Methods

### Study Design

A comparative effectiveness trial (CET) is being conducted to compare the effectiveness of the MobileMen app at increasing PA in African American men compared to Stridekick, a similar fitness app. The participants are assigned to one of the 2 arms: intervention (MobileMen) or comparator (Stridekick). The participants will use the assigned app on their personal smartphones for the duration of the 6-month trial. This study was registered with ClinicalTrials.gov (NCT05621044).

### Ethical Considerations

This protocol was approved by the Pennington Biomedical Research Center institutional review board on July 31, 2024 (approval 2021-052). All collected data will be deidentified before the analyses. All participants will complete an informed consent form and will receive US $200 compensation at the completion of their participation.

### MobileMen App

MobileMen is a mobile app tailored to the needs of African American men who aspire to increase their PA engagement [60]. MobileMen was developed using an extensive and iterative process described elsewhere [40]. The development of the MobileMen app was completed in July 2024 and is available for use on both iOS and Android platforms. See Table 1 for features of the MobileMen app.

**Table 1 table1:** Features of the MobileMen and Stridekick apps.

Feature	MobileMen app	Stridekick app
Syncs to Fitbit device	✔	✔
Display physical activity data	✔	✔
Message boards	✔^a^	✔
Goal setting	✔	✔
Challenges	✔	✔
Educational content (physical activity, nutrition, and behavior change articles)	✔	N/A^b^
Allows tracking of health metrics (blood pressure, blood glucose, body weight, and cholesterol)	✔	N/A
Incentives (virtual badges and tangible prizes)	✔	✔^c^
Designed with a behavior change theory framework	✔	N/A
Designed specifically for African American men	✔	N/A

^a^MobileMen is utilizing a private Facebook group for the message board feature during the comparative effectiveness trial.

^b^N/A: not applicable.

^c^Stridekick offers virtual badges but not tangible prizes.

### Comparator App

The Stridekick app is intended to increase PA in users through a variety of functions. Stridekick is a free app available on iOS and Android platforms. See Table 1 for Stridekick features.

### Participants

Eligibility criteria include self-identification as an African American male, a resting systolic blood pressure ≤159 mm Hg and a diastolic blood pressure ≤99 mm Hg (to reduce risk of exercise-induced cardiovascular events), free of significant medical problems that would impact their ability to engage in aerobic and/or resistance training, smartphone ownership, age > 30 years, and “low active” at baseline (defined as having an average daily accelerometer-assessed step count of <7500 steps) [61].

### Recruitment and Screening

Community-based efforts, including advertising at churches, health fairs, Young Men’s Christian Association, fraternities, social media posts, and advertisements on paid, owned, and earned media, are being used to recruit study participants. Potential participants undergo a telephone screening to assess initial eligibility.

### Study Visit 1

Men who meet the initial inclusion criteria are invited for an in-person or remote orientation visit with study staff. Study staff review the study protocol and facilitate an informed consent process. During this study visit, participants complete several baseline assessments, including a sociodemographic questionnaire and height, weight, pulse, and resting blood pressure measurements. We calculate BMI by using self-reported weight and height (kg/m^2^). Health-related quality of life is assessed using the 36-item short-form health survey, a widely used validated measure with strong internal consistency (Cronbach α > 0.80 across most domains) and robust evidence of construct and criterion validity and has been validated in African Americans [62,63]. To assess PA and dietary habits, participants complete the International Physical Activity Questionnaire and National Cancer Institute’s Automated Self-Administered 24-hour Dietary Assessment Tool, respectively [64,65]. Self-efficacy for fruit and vegetable consumption is measured with 7 items that measure participants’ confidence in their ability to consume fruits and vegetables in different contexts like when away from home or in a rush [66]. Self-efficacy for PA is measured using the Self-Efficacy for Exercise Scale [67]. SDT-based motivation for PA is measured using the Behavioral Regulations in Exercise Questionnaire v.3 [68,69]. This 24-item questionnaire assesses the 6 SDT subtypes of motivation, with each item scored on a 5-point Likert scale ranging from 0 (not true for me) to 4 (very true for me). The Behavioral Regulations in Exercise Questionnaire v.3 has strong internal consistency for each motivational subscale; it validly measures the different types of motivation and is predictive of exercise behavior [68,69]. Eligible participants receive a Fitbit to wear for 1 week to assess baseline PA levels.

### Study Visit 2

At the start of this remote or in person visit, study staff evaluate the Fitbit wear compliance. Participants who did not wear the Fitbit for at least 3 weekdays and 1 weekend day are required to rewear the device. Participants who self-report <60 minutes of moderate to vigorous PA on the International Physical Activity Questionnaire are eligible. Eligible participants are randomized to one of the 2 conditions, the MobileMen intervention group or the Stridekick comparator group, as directed by the next assignment letter contained in a randomized sequence of sealed and numbered envelopes. Using a computerized pseudorandom number generator, the statistician determines the randomization order in advance. The study coordinator reveals the randomization after the participant is deemed eligible. Project staff assist each participant in downloading the designated (MobileMen or Stridekick) app onto their smartphone, provide an app orientation, and assist in app navigation.

### Study Visit 3

At the conclusion of the 6-month intervention, participants complete all follow-up assessments (except for the Physical Activity Readiness Questionnaire for Everyone and demographic questionnaires) by using the same protocols as in study visit 1. Participants in both groups also complete additional measures such as a survey to assess their satisfaction with the mobile app and the System Usability Scale, a validated 10-item measure that provides a global view of the subjective usability for technology, to assess the app’s usability [70]. Participants also complete a brief interview with the study staff to collect feedback regarding suggestions for app improvement and users’ impressions of the app content.

### Outcome Measures

#### Primary Outcomes

The primary outcome measure for this study is change in step counts derived from the Fitbit collected before the intervention (week 0) and after the intervention (week 24).

#### Secondary Outcomes

Time spent in moderate to vigorous PA, also derived from the Fitbit preintervention and postintervention data, is a secondary outcome measure. Other secondary outcomes include changes in body weight, blood pressure, quality of life, and healthy eating index score. Daily PA engagement assessed with Fitbit Charge 6 is another secondary outcome measure. Using the Fitbit application programming interface, study staff will access participant daily steps, time spent engaging in PA, number of PA bouts, and minutes spent in each Fitbit-defined heart rate zone. Although Fitbit’s thresholds and algorithms are proprietary, research indicates that minutes categorized in Fitbit data as “active” (fairly active plus very active) generally correspond to what we consider moderate to vigorous PA [71-73]. Usability (using the System Usability Scale) and overall satisfaction with the MobileMen app are the additional secondary outcomes.

#### Potential Mediators

We will measure autonomous motivation and self-efficacy for PA preintervention and postintervention as potential mediators [66-70].

#### Potential Covariates

Demographic variables, including age, marital status, education, family income, occupation, and employment status, will be tested as potential covariates in our statistical models. We will also examine BMI and the self-reported measured blood pressure (mm Hg) at baseline as covariates.

### Sample Size and Power Calculation

A sample of 50 participants per trial arm was determined based on step count data from a recent meta-analysis [72]. The standard deviation in nondiseased populations on their step counts is 2000 to 3000 steps per day. When the sample size per group is 50, a 2-sided 95% CI for the difference of two means will extend to about 800 steps per day from the observed difference in means, assuming an SD of 2000 steps per day and the CI is based on the large sample *z* statistic. Doubling the sample reduces the half width of the CI to 560 steps per day, which reduces the half width by only 30% but disproportionately increases the recruitment time and difficulty. Within the 2 arms, we can estimate longer term adherence at 6 months with a width of a 2-sided 95% CI equal to 578 steps per day when the sample proportion adherent is 0.50, and the width shortens as the adherence increases.

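### The precision of the within-arm adherence proportion is given in steps per day, a unit that a proportion cannot have; the exact 95% CI width at 0.50 with 50 men is 0.289 (minor, sample size unaffected)

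*Protocol article*

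**What the plan says.** The Sample Size and Power Calculation section of the protocol article argues from precision. It takes the SD of step counts as 2000 to 3000 per day and computes with the lower end ("assuming an SD of 2000 steps per day"). For 50 men per group it gives a 95% CI half-width of about 800 steps per day for the difference in means, and 560 if the sample were doubled.

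The last sentence turns to another quantity: "Within the 2 arms, we can estimate longer term adherence at 6 months". Its precision is put at a "width of a 2-sided 95% CI equal to 578 steps per day when the sample proportion adherent is 0.50", and the sentence adds that "the width shortens as the adherence increases". No formula or interval method is given for this figure.

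**The concern.** The sentence identifies its own estimand twice. It conditions on a sample proportion of 0.50, and it says that the interval narrows as adherence rises, which is how a binomial interval behaves above 0.50. Both mark the quantity as a proportion, yet the width carries the unit of a step count. A CI for mean steps, at a fixed SD and sample size, would not depend on the proportion adherent.

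At stake is whether the figure can be used. Anyone who wants to know how well adherence at 6 months will be known in each arm cannot learn it from this sentence. Adherence does come up again: Statistical Analyses plans a close look at dropouts and noncompliant men and complier average causal effect models for app use.

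**Working it through.** **Inputs**, all from Sample Size and Power Calculation: 50 men per arm ("When the sample size per group is 50"); two-sided 95% confidence; adherent proportion 0.50, so x = 25 of n = 50; SD 2000 steps per day.

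**1. Exact interval for the proportion.** The Clopper-Pearson limits are beta quantiles:

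- lower = 2.5% quantile of Beta(x, n − x + 1) = Beta(25, 26) = 0.3553
- upper = 97.5% quantile of Beta(x + 1, n − x) = Beta(26, 25) = 0.6447
- width = 0.28945, that is 0.289

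**2. Reproducing the printed figure.** 0.289 × 2000 = 578, the stated number. Without rounding first, 0.28945 × 2000 = 578.9. The match therefore needs the width rounded to three decimals before multiplying. The product is not a CI for anything: the precision of a proportion does not depend on the SD of step counts. With the upper SD of 3000 the same product would be 0.289 × 3000 = 867.

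**3. Other proportion intervals at 25/50, multiplied by 2000.**

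| Method | Width | × 2000 |
|---|---|---|
| Exact | 0.289 | 578 |
| Wilson, continuity corrected | 0.286 | 571 |
| Wald | 0.277 | 554 |
| Jeffreys | 0.271 | 541 |
| Wilson | 0.267 | 534 |
| Wald, continuity corrected | 0.297 | 594 |

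Only the exact method gives 578.

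**4. Could it be an interval for one arm's mean steps?**

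- Full width: 2 × 1.96 × 2000/√50 = 1109
- Half-width: 554 (z) or 568 (t with 49 df)

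None is 578. The z half-width does reach 578 at n = 46, but the article mentions no such n. The sentence also says width, whereas the section says half width when it means that.

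**5. How the correct width changes with adherence** (exact, n = 50):

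| Observed proportion | Width |
|---|---|
| 0.50 | 0.289 |
| 0.60 | 0.284 |
| 0.70 | 0.267 |
| 0.80 | 0.237 |
| 0.90 | 0.185 |

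This agrees with the article's remark that the interval shortens.

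**6. The between-arm figures.** Half-width = 1.96 × SD × √(2/n):

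- n = 50 per arm: 1.96 × 2000 × √(2/50) = 784 (stated as about 800)
- n = 100 per arm: 1.96 × 2000 × √(2/100) = 554 (stated as 560)

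With t quantiles the values are 794 and 558. Both stated figures hold approximately.

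**The case against.** The best case for leaving the sentence alone is that it carries no weight. The section says that the size of each arm was determined from step-count data, and the figures behind that are the between-arm half-widths, which hold. The adherence sentence comes afterwards and describes what else this sample allows. The proportion adherent is not listed as a primary or secondary outcome under Outcome Measures, and the adherence-related analyses do not use this width. All of that stands, and it is why the point is minor. It does not make the printed figure right.

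Two stronger readings are tempting:

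- A reader might infer that the error undermines the choice of 50 per arm. The text does not support this: the size is tied to step counts, and that arithmetic reproduces.
- A reader might infer that the article overstates the precision of mean steps about twofold, since 578 is roughly half of 1109. But the sentence speaks of adherence and of a proportion and claims nothing about mean steps in one arm. That anyone would be misled in this way is speculation.

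It is also fair to object that the origin of 578 is inferred. No derivation is shown, and the unrounded product is 578.9, which would print as 579. The product of 0.289 and 2000 is the likeliest source, not an established one. The unit is wrong whatever the source.

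**Conclusion.** The sentence is wrong as written, and the error is minor. A 95% CI width for a proportion cannot be 578 steps per day. At an observed proportion of 0.50 with 50 men, the exact width is 0.289, about 29 percentage points (35.5% to 64.5%).

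That the unit is wrong follows from the text alone. The replacement value rests on two assumptions: that the exact method was intended, which the article does not say, and that all 50 men in an arm contribute. The section gives no attrition figure; with fewer evaluable men the interval would be wider. With the other methods tabulated above, the width at 0.50 lies between 0.267 and 0.297, so the choice of method does not alter the conclusion.

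Sample size, outcomes and primary analysis are unaffected.

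**What to change.** Replace the last sentence of Sample Size and Power Calculation with, for example:

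*Within each arm (n=50), the exact (Clopper-Pearson) 2-sided 95% CI for the proportion adherent at 6 months has a width of 0.289 (0.355 to 0.645) when the observed proportion is 0.50, narrowing to 0.237 at 0.80.*

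The step unit goes from that sentence. Three decimals are worth keeping so that the limits and the width agree to within rounding: limits rounded to 0.36 and 0.64 differ by 0.28, which would not match a width of 0.29. The sponsor should confirm which interval method was used; if it was not the exact one, the numbers should be replaced to suit.

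The cost is one sentence. No new data are needed and trial conduct does not change.
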